## Abstract

**Background:**

Constipation is a frequent problem in adults with Prader–Willi syndrome. Certain probiotics have been shown to improve transit and gastrointestinal symptoms of adults with functional constipation. The aim of this study is to determine the effect of daily consumption of *Bifidobacterium animalis* ssp. *lactis* B94 (*B. lactis* B94) on stool frequency, stool form, and gastrointestinal symptoms in adults with Prader–Willi syndrome.

**Methods:**

Adults with Prader–Willi syndrome (18–75 years old, *n* = 36) will be recruited and enrolled in a 20-week, randomized, double-blind, placebo-controlled, crossover study. Study subjects will be randomized to *B. lactis* B94 or placebo each for a 4-week period, preceded by a 4-week baseline and followed by 4-week washouts. Subjects will complete daily records of stool frequency and stool form (a proxy of transit time). Dietary intake data also will be collected. Stools, one in each period, will be collected for exploratory microbiota analyses.

**Discussion:**

To our knowledge, this is the first randomized controlled trial evaluating the effectiveness of *B. lactis* in adults with Prader–Willi syndrome. The results of this study will provide evidence of efficacy for future clinical trials in patient populations with constipation.

**Trial registration:**

ClinicalTrials.gov (NCT03277157). Registered on 08 September 2017.

**Electronic supplementary material:**

The online version of this article (10.1186/s13063-018-2648-x) contains supplementary material, which is available to authorized users.

## Background

Prader–Willi syndrome (PWS) is a genetic disorder due to the non-expression of specific genes from the chromosome 15q11.2-q13 region [1]. The lack of imprinted genes occurs by three mechanisms, namely deletion of the 15q11.2-q13 region (found in 65–75% of individuals), maternal uniparental disomy (found in 20–30% of individuals), and an imprinting defect when the genomic region that manages the imprinting process is defective (1–3% of individuals) [1]. The estimated prevalence of PWS is 1/10,000 to 1/30,000 people [1]. At an early age, infants have severe hypotonia and feeding difficulties followed by weight gain and subsequent hyperphagia during childhood [1]. Due to altered body composition and depressed basal metabolic rate in adults with PWS [2], lifelong energy restriction is required to circumvent the development of morbid obesity [3].

Constipation is a common problem for individuals with PWS. A study of adults with PWS showed that 40% of these individuals have constipation symptoms, including having less than three defecations per week, sensation of anorectal obstruction, straining during defecation, and having hard stools [4]. Although adequate dietary fiber may be achievable in children with PWS [5], this may be a challenge in adults with PWS, particularly given their low energy needs and, thus, limited food choices. Certain probiotics, “*live microorganisms that when administered in adequate amounts confer a health benefit to the host*” [6], have been shown to improve constipation symptoms in otherwise healthy adults. Probiotics have been shown to significantly decrease transit time, increase stool frequency, and improve stool consistency, particularly *Bifidobacterium lactis* strains [7]. This study will build on previous literature reporting on the efficacy of probiotics in adults with constipation and will examine the effect of *Bifidobacterium animalis* ssp. *lactis* B94 (*B. lactis* B94) in adults with PWS. The aim of the study is to determine the effect of *B. lactis* B94 on stool frequency, stool form (a proxy for transit time), gastrointestinal (GI) symptoms, and fecal microbiota in adults with PWS. It is hypothesized that *B. lactis* B94 will increase stool frequency, decrease the percentage of slow transit stools, and improve GI symptoms. The primary outcome of the study is weekly stool frequency (difference between treatments), whereas secondary outcomes are weekly stool frequency (percentage change from baseline), stool form (percentage change in slow transit Bristol Stool Form Scale (BSFS) 1 and 2 [8] from baseline and between treatments), GI symptoms, and compliance (recorded intake of the provided and remaining supplements).

## Methods

### Design

A 20-week randomized, double-blinded, placebo-controlled crossover study will be carried out (Fig. 1). Adults with genetically confirmed PWS will be recruited. Subjects will complete a 4-week baseline period during which data on daily stool frequency and stool form will be collected. Dietary intake data (food record) will be obtained during the baseline period and subjects will collect a single stool. Subjects will be randomized on or about day 29 and will consume one capsule per day of *B. lactis* B94 or placebo for 4 weeks, followed by a 4-week washout, 4 weeks on the alternative treatment, and a second 4-week washout.

**Fig. 1 Fig1:**
[figure not shown]
Study Design (*DQ* daily questionnaire, *GSRS* Gastrointestinal Symptom Rating Scale, *B. lactis* B94 *Bifidobacterium animalis* ssp. *lactis* B94)

During the intervention and washout periods, subjects will continue a daily record of stool frequency, stool form, and compliance. In addition, subjects will complete the Gastrointestinal Symptom Rating Scale (GSRS) [9, 10] during weeks 4, 8, 12, 16, and 20. During these same weeks, dietary intake data (food record) and single stools will be collected per period. Subject demographics, height, and weight will be taken at baseline, and body weight during weeks 8, 12, 16, and 20. Figure 2 provides the schedule of enrollment, interventions, and assessments to be completed. This paper follows the Standard Protocol Items: Recommendations for Interventional trials (SPIRIT) (Additional file 1) and the World Health Organization Trial Registration Data Set (Additional file 2).

**Fig. 2 Fig2:**
[figure not shown]
Schedule of enrollment, interventions, and assessments as per Standard Protocol Items: Recommendations for Interventional trials (SPIRIT)

### Randomization and blinding

A computer-generated random number sequence will be used for allocation. Randomization will be by sealed envelope method, prepared by an individual not affiliated with the study. No blocking or stratification will be performed. The principal investigator (PI) will conduct the randomization and distribution of the investigational product (IP)/placebo. Researchers, trial participants, data analysts, and all staff members at the study sites will remain blinded for the duration of the study and until the statistical analyses are completed.

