### Intervention

Subjects will be randomized to consume either *B. lactis* B94 or placebo for a 4-week period. A 4-week supply of the *B. lactis* B94 or placebo will be given during the study visit at the start of the intervention periods. Capsules will be stored at refrigerator temperature. The IP will be *B. lactis* B94 at a dose of 15 billion colony forming units (CFU) in Veggie capsule #1 made with potato starch and magnesium stearate, and the placebo will contain potato starch and magnesium stearate (Lallemand Health Solutions Inc., Mirabel, Canada). Prior to delivery to the study site, the IP and placebo will be coded by an unblinded employee of the manufacturer. The IP and placebo will be coded with five codes each, so in the event of an adverse event that requires unblinding of the effected subject, information about most remaining subjects will remain blinded. The IP and placebo capsules will be stored in a locked refrigerator at the research site with access limited to the PI and study coordinator.

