### Sample size determination

For the power calculation, mean differences between the treatment group and the placebo group were obtained from Ishizuka et al. [15], who reported that, for constipated subjects, the mean frequency of bowel movements per week was 3.8 at baseline, 4.4 in the second week for those on placebo, and 5.1 in the second week for those on treatment. Data were simulated for each of the two experimental designs for 10,000 subjects assuming correlated Poisson random variables with mean weekly bowel movements as given above. Either the weekly totals as simulated or the averages of the weekly totals for each period (baseline, intervention) were used in subsequent analyses. For the simulations, all washouts were assumed to have the same mean as the placebo (4.4 bowel movements/week) and no temporal trend within each intervention or washout period was assumed. A correlation of 0.35 for the repeated observations on a subject was assumed. This value was obtained from previous studies involving measurement of weekly total bowel movements such as that of Baird et al. [16]. All power analyses were based on using a type I error rate of 0.05 and no correction for possible multiple comparisons. A cross-over study with five time periods, i.e., 4 weeks of baseline, 4 weeks on one treatment, 4 weeks of washout, 4 weeks on the alternative treatment, and 4 weeks post-treatment, was considered. Within each time period, the weekly totals to obtain an average total within each period for each subject were averaged. Hence, the value for any time period for a subject is the mean of the 4 weekly totals. Hypothesis testing included the F-tests in the ANOVA table for ‘Period’ and a *t* test of the difference between the product and placebo. The recommended sample size for this model is 26 to determine a difference between treatments. If the weekly means and then the treatment differences by averaging the least squares means are tested after analysis, the same sample size is required, confirming the appropriate sample size of 26. A washout of 4 weeks is expected to be sufficient to minimize any carryover effects. However, with a possibly high dropout rate of approximately 25% (due to the length of the study), a sample size of 36 is targeted. The targeted sample size is feasible as recruitment will be from a population that includes individuals participating in residential programming and those residing in the community at large.

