### Statistical analysis

For the primary outcome of stool frequency, data will be analyzed using a general linear mixed model with intervention, week, period, sequence, and the interactions of period, sequence and intervention with week (weekly data), as the main fixed effects. A random effect of subject will be included in the models. Pairwise tests and post-hoc analyses will be conducted using the Tukey–Kramer method. Kenward–Roger adjustments for the denominator degrees of freedom will be performed to adjust for bias in the covariance estimates for the random effect.

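### Unblocked randomisation of 36 subjects leaves the crossover sequence split to chance: a small, largely avoidable loss of precision, with no bias

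*Protocol article*

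**What the plan says.** The Randomization and blinding section describes simple randomisation: "A computer-generated random number sequence will be used for allocation", in sealed envelopes prepared by someone outside the study, and "No blocking or stratification will be performed". It adds that "The principal investigator (PI) will conduct the randomization and distribution of the investigational product (IP)/placebo", while researchers, participants, analysts and site staff stay blinded until the analyses are finished. The Intervention section has the manufacturer label each product with five codes, so that breaking one code leaves most other subjects blinded.

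Under Sample size determination, "The recommended sample size for this model is 26 to determine a difference between treatments", and "with a possibly high dropout rate of approximately 25% (due to the length of the study), a sample size of 36 is targeted". Under Statistical analysis, stool frequency is analysed with a "general linear mixed model with intervention, week, period, sequence" and the interactions of period, sequence and intervention with week, plus a random subject effect. No allocation ratio, target power or sidedness is stated.

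**The concern.** In a two-sequence crossover with period and sequence in the model, the treatment effect is half the difference between the two sequences' mean within-subject differences. Its variance is proportional to 1/n1 + 1/n2, where n1 and n2 are the numbers in each sequence. For a fixed total this is smallest when n1 = n2. Unrestricted allocation of a few dozen subjects can miss that optimum by enough to cost information. The Discussion describes the population as limited, so lost information is hard to replace by recruiting more. What is at stake is precision only: the model removes period and sequence effects whatever the split.

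**Working it through.** **Inputs from Sample size determination.** Weekly means were "4.4 in the second week for those on placebo, and 5.1 in the second week for those on treatment", a difference of 0.7. Weekly totals are Poisson (variance equals mean), the correlation between a subject's repeated observations is 0.35, the unit is the mean of four weekly totals, and the type I error rate is 0.05.

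**Assumptions not in the document.** 1:1 allocation, a two-sided test, and dropout unrelated to sequence.

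**Step 1: reproduce the planned size.** With an exchangeable correlation, the variance of a subject's B94-minus-placebo difference is

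(4.4 + 5.1)(1 + 3 × 0.35)/4 − 2 × 0.35 × √(4.4 × 5.1) = 1.553, so SD 1.246.

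For 80% power (assumed), the normal approximation gives n = 25 and the noncentral t with n − 2 degrees of freedom gives 27. The stated 26 lies between them; its power is 78.5% at 13:13. At 90% power the answer would be 36 evaluable, which does not match, so about 80% is the likely target. For dropout, 26/0.75 = 34.7, or 35, against 36 stated; 36 × 0.75 = 27 completers.

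**Step 2: cost of an uneven split.** Var = (1.553/4)(1/n1 + 1/n2). Efficiency relative to an even split is 4·n1·n2/N² = 1 − ((n1 − n2)/N)². Under simple randomisation n1 is Binomial(N, 0.5) and E(n1 − n2)² = N, so expected efficiency is 1 − 1/N: 0.972 at 36 and 0.963 at 27.

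| Split | Chance of this or worse | Efficiency | Power at this split |
|---|---|---|---|
| N = 36, 18:18 | – | 1.000 | 90.6% |
| 14:22 | 24.3% | 0.951 | 89.1% |
| 13:23 | 13.3% | 0.923 | 88.2% |
| 12:24 | 6.5% | 0.889 | 87.0% |
| N = 27, 13:14 | – | 0.999 | 80.0% |
| 9:18 | 12.2% | 0.889 | 75.3% |
| 8:19 | 5.2% | 0.834 | 72.7% |

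Averaged over the binomial distribution, power is 89.7% at N = 36 and 78.5% at N = 27.

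**Step 3: what blocking recovers.** At 36 it restores efficiency to 1.00 for an 18:18 split, so the gain is 90.6% − 89.7% = 0.9 points. At 27 completers, dropout unbalances a blocked trial as well. Starting from 18:18 and losing 9 at random, the number left in one sequence is hypergeometric with variance 27 × 0.25 × 9/35 = 1.736. Then E(n1 − n2)² = 4 × 1.736 = 6.94, and expected efficiency is 1 − 6.94/27² = 0.990. Expected power is about 79.7%. The recoverable part is therefore 0.990 − 0.963 = 0.027 in efficiency and about 1.2 points of power. The 8:19 tail disappears: losing all 9 from one sequence of 18 leaves 9:18 at worst.

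**Step 4: range for the unstated power.** If the variance is instead scaled so that 26 subjects give exactly 80%, expected power at N = 36 is 90.8% against 91.6% balanced, and at 27 it is 80.0% against 81.5%. If 26 gives 90%, the pairs are 96.7% against 97.1% and 90.0% against 91.1%. The cost stays between about 0.4 and 1.5 points.

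**The case against.** Simple randomisation is valid, openly stated and unbiased, and an article need not give the reason for it. The average cost is about one subject in 36. All of that stands, and it fixes the size of the point.

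Four stronger readings are tempting and not supported.

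- **That a marked imbalance is to be expected.** A 2:1 split or worse has a 6.5% chance at 36, and even then the standard error rises by only 6.1%.
- **That leaving out blocks brings no benefit.** It makes each allocation independent of the others, which has some value when the PI both randomises and hands out product. The protocol also foresees breaking a single code after an adverse event. In a block of two, learning one subject's sequence would reveal the partner's; in larger blocks it would shift the odds. The risk is small here, because product is coded, staff are blinded, block sizes would be undisclosed and every subject receives both treatments, but it is not nil.
- **That the trial is sized at the bare minimum, with power falling from 80%.** The protocol names no target power and aims for 36 against a requirement of 26. Power near 73% needs the full dropout allowance and an unlucky split together.
- **That blocking would recover the whole 3.7% loss at 27 completers.** Dropout limits this to about 2.7%.

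**Conclusion.** The point holds as a minor inefficiency. The sequence split is left to chance although the precision of the primary contrast depends on it. The expected loss is 2.8% of the information at 36 subjects, or 0.9 points of power on the planning inputs, and about 1.2 recoverable points at 27 completers. The clearer gain is removal of the 5% chance that the completers split 8:19 or worse. The probabilities of each split and the efficiencies rest on 1:1 allocation and, at 27, on dropout unrelated to sequence. The power figures also rest on a two-sided 5% test and on the protocol's effect, Poisson variance and correlation of 0.35. The validity of the treatment comparison is not in question.

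**What to change.** Have the independent person who prepares the envelopes generate the list, or the part not yet used, in permuted blocks of mixed and undisclosed size across the two sequences, and replace the sentence that rules out blocking. Subjects already randomised, the treatments, the outcomes and the analysis model are unaffected.

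The costs are a small protocol amendment and slightly less unpredictability, chiefly if one subject's code is broken. The gain shrinks with time, because imbalance already accrued stays. If, for illustration, 18 of 36 had been randomised, the remaining expected loss would be 18/36² = 1.4% instead of 2.8%, a gain of about half a subject. The Trial status section has recruitment running from December 2017 to December 2018, so the change is worth making early or not at all. If enrolment is complete, it is enough to report the achieved split, at randomisation and among completers.

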### Participants

Adults with PWS, residing in residential programs and in the community at large in the state of Florida, United States, will be recruited for this study (*n* = 36). Potential subjects will be identified and contacted by their physician. The study coordinator will then meet with interested individuals, provide them with a full description of the study, and enroll those eligible. Potential subjects will be included if they have a genetically confirmed diagnosis of PWS and are 18–75 years of age, willing to have height and weight measured and to provide demographic information (e.g., age, race, sex), willing to consume *B. lactis* B94 and placebo each for a 4-week period, willing to complete a daily record of stool number and form throughout the 20-week period, willing to complete the GSRS monthly, and willing to provide information about their dietary intake every 4 weeks. Potential subjects will be excluded if they have a milk protein allergy, are currently taking medications for diarrhea or probiotics supplements and do not want to discontinue prior to the start of the baseline period (i.e., those that discontinue will be included), and were previously or are currently being treated for GI diseases, including gastric ulcers, Crohn’s disease, celiac disease, ulcerative colitis, or GI cancer. Subjects will receive their usual clinical care throughout the study.

### Intervention

Subjects will be randomized to consume either *B. lactis* B94 or placebo for a 4-week period. A 4-week supply of the *B. lactis* B94 or placebo will be given during the study visit at the start of the intervention periods. Capsules will be stored at refrigerator temperature. The IP will be *B. lactis* B94 at a dose of 15 billion colony forming units (CFU) in Veggie capsule #1 made with potato starch and magnesium stearate, and the placebo will contain potato starch and magnesium stearate (Lallemand Health Solutions Inc., Mirabel, Canada). Prior to delivery to the study site, the IP and placebo will be coded by an unblinded employee of the manufacturer. The IP and placebo will be coded with five codes each, so in the event of an adverse event that requires unblinding of the effected subject, information about most remaining subjects will remain blinded. The IP and placebo capsules will be stored in a locked refrigerator at the research site with access limited to the PI and study coordinator.

### Compliance

Study subjects will be asked to return unused capsules at the end of each intervention period to document compliance. Compliant subjects will be defined as more than 80% of supplement intake.

Recovery of *B. lactis* B94 from fecal samples will also be used to assess compliance. Study coordinators will be in frequent contact with the study participants throughout the study to promote compliance to the protocol.

### Withdrawal criteria

Subjects will be free to withdraw their consent and to stop participating in the study at any time. Subjects may be withdrawn from the study by the PI for non-compliance (e.g., do not consume the study capsules). Consent forms, given to all subjects, will specify the contact person in the case of adverse events occurring during the study. In a circumstance that a professional intervention is necessary due to an adverse event, the PI will contact the study’s affiliated physician and appropriate authority or organization pertinent to the circumstance of the event. If deemed necessary, the manufacturer of the capsules will be contacted to unblind the subject (one of 10 codes). As there are no known risks for consuming the probiotic, *B. lactis* B94, no negative side effects or adverse events are expected and, thus, no data monitoring committee is needed.

### Outcomes

#### Stool form

Stool form will be assessed using the BSFS, a simple tool for estimating intestinal transit time [8]. The BSFS classifies stools into seven categories, including type 1, separate hard lumps, like nuts; type 2, sausage-shaped, but lumpy; type 3, like a sausage but with cracks on the surface; type 4, like a sausage or snake, smooth and soft; type 5, soft blobs with clear-cut edges; type 6, fluffy pieces with ragged edges, a mushy stool; type 7, watery, no solid pieces [8]. These types are categorized into slow transit (types 1 and 2), normal transit (types 3–5), and fast transit (types 6 and 7).

#### GI symptoms

GI symptoms will be assessed using the GSRS, a 7-point scale that evaluates symptoms of GI disorders, where 1 represents no discomfort at all and 7 represents very severe discomfort over the past week [9, 10]. Symptoms of the GSRS are grouped into five GI syndromes, which are abdominal pain, reflux syndrome, diarrhea syndrome, indigestion syndrome, and constipation syndrome.

#### Microbiota analysis

Subjects will be asked to collect one stool each during the baseline, intervention 1, washout 1, intervention 2, and washout 2 periods. Subjects will be provided with Fisherbrand^®^ commode collection kits for stool collection. Samples will be processed and appropriately stored in the lab within 6 h after defecation. Stool samples will be analyzed for changes in microbiota. Changes in the concentration of *Lactobacilli* and *Bifidobacteria* genera as well as *Bifidobacterium animalis* sp. *lactis* will be measured in fecal samples by real-time PCR (qPCR).

Total DNA will be extracted from homogenized fecal samples using the QIAamp^®^ Fast DNA Stool Mini Kit (Qiagen, Hilden, Germany) as per the manufacturer’s instructions, with minor modifications, i.e., two 0.05 M phosphate buffer washes prior to the addition of InhibitEX (Qiagen) and a 1 mm zirconia/silica bead beating step (~250–350 mg/tube, 4 m/s for 1 min × 3) before centrifugation of samples to pellet stool particles. Purified DNA will be further processed for qPCR and 16S rRNA gene amplicon sequencing.

For qPCR, template DNA for standard curves will be generated by spiking feces with a bacterial suspension consisting of lyophilized bacterial powder (Lallemand Health Solutions) in HyClone phosphate buffered saline. Total cell count of each bacterial suspension will be determined by flow cytometry. Feces will be spiked with a volume equivalent to 10^9^ bacteria, and then subjected to DNA extraction as described above.

Quantification of *Lactobacilli*, *Bifidobacteria*, and *Bifidobacterium animalis* sp. *lactis* will be performed by qPCR using the ViiA™ 7 Real-Time PCR System (Thermo Fisher Scientific). Standard curves will be generated by serially diluting DNA from spiked feces. DNA samples to be quantified will be diluted in molecular biology grade water prior to qPCR.

The qPCR reaction mixture will consist of the appropriate primers, 1X SYBR^®^ Select Master Mix (Thermo Fisher Scientific), and diluted DNA. Standard curve samples will be run in duplicate and unknown samples will be tested in triplicate. Cycling conditions will consist of initial incubations, followed by 40 cycles of denaturation, annealing, and extension. A dissociation curve analysis (60°C to 95°C) will also be performed to ensure amplification specificity of the primers.

Libraries for sequencing will be prepared according to Illumina’s 16S Metagenomic Sequencing Library Preparation guidelines (Part # 15044223 Rev. B), with the exception of using Qiagen HotStar MasterMix for the first PCR (‘amplicon PCR’) and halving reagent volumes for the second PCR (‘index PCR’). As per Illumina’s guidelines, template-specific primers will target the V3-V4 region of the 16S rRNA gene (PMCID: PMC3592464) [11]. Resulting sequence reads will be analyzed through the National Research Council’s (Montreal, Canada) 16S rRNA gene amplicon analysis pipeline, as previously described [12, 13]. Reads will be QCed, paired-end assembled, and clustered at 97% similarity. Taxonomic summaries and alpha (observed) and beta (weighted or unweighted UniFrac and Bray-Curtis distances) diversity metrics, statistical analysis, and taxonomic classifications will be computed using QIIME software [14] and downstream analyses will be performed with in-house Perl and R scripts at the National Research Council.

